**STUDY FLOW CHART: WHOLE SAMPLE**

| STUDY EXAMINATION                                                   | Day 1/V1
Inclusion visit
(in the health centre) | Day 5 (± 2 days)/V2
(Contact by the CHA) | Unforeseen
Visit | End of 28 day
follow-up |
|---------------------------------------------------------------------|-------------------------------------------------------|---------------------------------------------|---------------------|----------------------------|
| Demographic data, sex and weight                                    | X                                                     |                                             |                     |                            |
| Informed consent and recruitment criteria                           | X                                                     |                                             |                     |                            |
| Physical examination / Malaria symptoms / Other symptoms            | X                                                     |                                             | x                   |                            |
| Rapid Diagnostic Test/microscopy to confirm diagnosis (if feasible) | X                                                     |                                             |                     |                            |
| Thick blood smear collection for further evaluation                 | X                                                     |                                             | x                   |                            |
| Previous medications (last month)                                   | X                                                     |                                             |                     |                            |
| Medical history                                                     | X                                                     |                                             |                     |                            |
| Prescription of Eurartesim®                                         | X                                                     |                                             |                     |                            |

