| Prescription of Eurartesim®                                                               | X                                                     |                                                   |                     |                         |
| AE recording                                                                              | X                                                     | X                                                 | X                   | X                       |
| ECG recording                                                                             | x (*)                                                 | x#                                                | x (**)              |                         |
| Concomitant medications                                                                   | X                                                     | X                                                 | X                   |                         |
| Plasma sample collection for PQ concentration                                             | X                                                     | x#                                                | X                   |                         |

(\*) Triplicate ECG will be recorded, without causing delay in the treatment of malaria

(\*\*) If clinically significant abnormalities are observed at Day 7

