### 3.3 Malaria in Burkina Faso, Mozambique, Ghana and Tanzania

#### Ghana

Malaria is the leading cause of morbidity and mortality reported in health facilities in the Northern areas where Navrongo HDSS is located. **Malaria transmission occurs during most months of the year but there is a distinct seasonal pattern with the peak of**

transmission coinciding with the period of the major rains (May – October) and the dry season (November – April) seeing very low rates of malaria infection. Transmission has been estimated to be 418 infective bites per person per year. The main malaria vectors are *A. gambiaes.l* and *A. funestus* constituting about 94.3% of the vector population. The predominant parasite species is *P. falciparum* (accounting for more than 90% of all infections). *P. malariae* is seen in a small proportion of infections (less than 5%) and some mixed infections of *P. falciparum* and *P. malariae*. *P. ovale* is rarely seen and no *vivax* is seen. The incidence of clinical malaria also shows some seasonality with an incidence density of infection varying from five cases per person- year in the dry season to over seven cases per person-year in the wet season. In a just concluded study of malaria morbidity and mortality in a birth cohort of children in the district (n=2200), 38.9% of all admissions in this cohort was due to malaria with malaria accounting for 50.9% of all hospital visits made by cohort members (unpublished data).

In the middle belt of Ghana where the Kintampo HDSS is located, The parasite prevalence in children <10 years of age is >50% all year round and the incidence of clinical malaria among children less than 5 years is about 7 episodes per child per year. The main vectors for transmission of malaria are *Anopheles gambiae* and *A. funestus* and the transmission is perennial but peaks between April and October. The annual entomological inoculation rate was 269 infective bites per person per year in 2005. Malaria is diagnosed by clinical suspicion and confirmed with rapid diagnostic test or microscopy. The first line treatment for malaria is artesunate-amodiaquine or arthemether-lumefantrine for uncomplicated malaria and quinine for complicated malaria. Chemical shops are the first point of call during a child's febrile illness and use of traditional medicine and left over drugs at home is also common in the study area.

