### **4.2 Secondary objectives**

- 4.2.1 Main secondary

- Intensive assessment of a nested subset of **about 1,000** patients to evaluate the effect of the administration of Eurartesim® on blood biochemistry, full blood count and QTc intervals.
- QTc interval and piperazine concentration relationship will also be investigated in all the **nested 1,000** patients.

- 4.2.2 Other secondaries

- Description of the prevalence of *Plasmodia* species (*falciparum*, *vivax*, *ovale*, *malariae*) as confirmed by blood smear results in the nested subset of 1,000 patients and retrospective comparison of the tolerability profiles between the two sub-populations of patients infected with *Plasmodium falciparum* and patients infected with other *Plasmodia*.
- Assessment of the relationship between the occurrence of adverse events and the administration of concomitant medications will be made in the subset of 1,000 patients.

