### 7.2.2 Examination and data collection at inclusion

In case the patient meets the protocol selection criteria and agrees to participate in the study, the following procedures will be followed:

- An informed consent form will have to be signed and will be filed with the registry.
- The HF will assign a patient ID number to the patient, visit the patient as usual and record the following data:
  - On the patient chart: last name, first name, full address (village/neighbourhood), registration number and patient ID number.
  - On the rest of patient chart: the other information collected during this visit, i.e.:
    - Demographic data of the patient: patient ID number, initials, age, sex, weight and body temperature.
    - Intake of anti-malarial drugs during the 4 weeks before inclusion.
    - Intake of any other treatment including traditional treatments, during the 2 weeks before inclusion.
    - Concomitant treatments and treatments prescribed when visiting the centre.
    - Malaria and associated disease symptoms will also be reported.
    - Confirmation that a thick blood smear identified by the patient's ID number and the date of blood withdrawal has been taken and prepared for later reading.
    - Confirmation that a blood sample for haematology, blood chemistry and PK (where foreseen) has been drawn in the subset of patients more closely evaluated; and that in the same subgroup a triplicate ECG has been recorded. Results of the ECGs local readings and laboratory examinations will be reported as soon as possible on the chart (copy of the results have to be stored at site).
    - Eurartesim® treatment administration time. Dosage will be defined according to the weight of the patient. The patient will be instructed to take the medication with water, between meals as described in section 5.3. In all the 10,000 patients the first dose of the study drug will be directly administered at the facility and time of administration and time of last food consumption will be annotated.

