### 7.2.3 Follow-up visits/contacts and clinical tolerability follow-up questionnaire

At Day 5 ( $\pm 2$  days) (after administration of the last Eurartesim® dose) following the inclusion date, the community health agent (CHA) will contact the patient at home. A further visit at the patient's home will be scheduled by the community health agent in all the cases in which the information collected during the telephone contact should be considered incomplete or unreliable ones.

He/she will then fill-in the second part of the chart (in triplicate) and report:

- His/her own 4 digit identification number (first two digits are the number of the health centre he/she is attached followed by a 2 digit number which will be assigned to him/her when the study starts).
- Date of the visit/contact.
- Clinical condition (recovered status or continuation of the illnesses).
- Compliance with the prescribed Eurartesim® treatment and in case, number of tablets of Eurartesim® not taken; an explanation of the reason why the treatment was not followed should be provided.
- Description of the symptoms experienced by the patient in case of a positive answer to the question: *“Have you noticed any unusual event/symptom since your last visit at the centre?”* Collect date of first manifestation of this/these event(s), symptom(s), intensity, treatment dis-/continuation, and evolution, in the specific section of the patient chart dedicated to the collection of Adverse Events.
- Current treatments, if taken.

In case, during his/her contact, the CHA assess that an occurred event is serious and/or severe, or detects an adverse event of special interest (see section 8.5), he/she should contact the HA and transfer the patient to the health facility in order to be examined. If necessary in the opinion of the HA, he/she should contact the investigators so that they can visit the patient and exactly define the status of the event and the causality. If the adverse event belongs to the cardiovascular category, an ECG will be performed. In addition, a thick blood smear will be prepared (for future analysis). In that event, a specific adverse event report form will be completed by the HA or the investigators.

The patient will receive first care treatment. In case any other treatment is prescribed by a HA staff or the study doctor, it will be reported on the patient chart.

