All the patients will be instructed to refer to the CHA or the designated HF in the HDSS should any adverse event occur within the 28 day after the start of the Eurartesim® administration.

In addition the regional hospital will be alerted to check referrals for participation in the study, and there will be a collection on a regular basis of any data related to patients who are treated in regional hospitals who have taken part in the study.

The patients recruited in the 1,000 subset group will be reviewed at the HF on day 3 (last day of administration of Eurartesim® dose). Before the Eurartesim® administration, a blood sample will be collected for PQ concentration evaluation (in all the 1000 subgroup of patients) and a single ECG will be recorded. The last dose of Eurartesim® will be directly administered by the HA to the patient after documentation that the last meal was taken more than 3 hours prior to administration. Three to four hours after the Eurartesim® administration, a blood sample for haematology, blood chemistry and PQ concentration will be collected and a triplicate ECG will be recorded.

The following information will be recorded in the second part of the chart (in triplicate):

- The HA or study team staff will record his/her own 4 digit identification number (number of the health centre he/she is attached followed by a 2 digit number which will be assigned to him/her when the study starts).
- Date of the visit.
- Clinical condition (recovered status or continuation of the illnesses).

- Time of drug administration
- Compliance with the Eurartesim® treatment during the three day treatment.
- Results of the ECGs and laboratory examinations
- Occurrence of Adverse Events.

The patients recruited in the subset will have to come back at the health facility on day 7 to perform a further single ECG, a blood sample drawing for haematology and biochemistry determinations and to collect, if any, Adverse Events occurred.

Again the HA or study team staff will record his/her own 4 digit identification number and record the appropriate information on the patient chart.

All the patients will be instructed to refer to the CHA or the designated HF in the HDSS should any adverse event occur starting from the 7 day visit/contact and the 28 day after the start of the Eurartesim® administration.

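### The follow-up chart contents in section 7.2.3 do not match the concomitant-medication row of the flow charts, so short drug courses begun after Day 1 can go unrecorded

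*Protocol*

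**What the plan says.** **Flow charts (protocol summary).** The row "Concomitant medications" is marked in both charts at Day 1, at the scheduled follow-up (Day 5 ± 2 for the whole sample, Day 3 and Day 7 for the nested study) and at unforeseen visits. The end-of-28-day cell is blank in both.

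**Inclusion (section 7.2.2).** For every patient the chart records "Concomitant treatments and treatments prescribed when visiting the centre", antimalarial use over the preceding 4 weeks, and "Intake of any other treatment including traditional treatments, during the 2 weeks before inclusion".

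**Follow-up (section 7.2.3).** The main-group contact list has one medication item: "Current treatments, if taken". Treatment prescribed by health staff or the study doctor also goes on the chart. For the nested Day 3 visit, the list introduced by "The following information will be recorded in the second part of the chart (in triplicate" covers staff number, date, clinical condition, dosing time, compliance, ECG and laboratory results, and adverse events. It has no medication item. The Day 7 text names an ECG, blood samples and adverse events, and otherwise leaves staff to record whatever is appropriate.

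**Analyses that use these data.** Section 4.2 sets a secondary objective on adverse events in relation to concomitant drugs: "the administration of concomitant medications will be made in the subset of 1,000 patients". Section 9.2 relates adverse events of special interest to previous and concomitant drug use in the whole sample and in the subset, and in the subset models QTc on all recorded covariates.

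**The concern.** The same contact treats events and drugs differently. The adverse-event question in 7.2.3 covers the whole interval since the patient was last at the centre and asks for the date of onset. The medication item covers only the moment of contact. Section 7.1 puts that contact after the last dose, so a drug used on Day 2 or Day 3 and then stopped is outside the question as worded.

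In the nested group the visit text is silent on medications, although this is the group in which the objective on concomitant drugs is set.

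The days in question are those of dosing and shortly after, when piperaquine has accumulated; section 3.2 gives an accumulation factor of about 3 over the three-day course. An analysis plan can define drug classes and exposure windows, but it cannot recover a drug that nobody asked about.

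**Working it through.** The protocol states no figure on this point, so there is none to reproduce. The check is a comparison of texts, followed by an illustration on stated assumptions.

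**1. Flow charts against chart contents**

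| Contact | Flow chart | Section 7.2.2 or 7.2.3 | Match? |
|---|---|---|---|
| Day 1, all patients | Marked | Concomitant, newly prescribed and prior treatments, including traditional ones | Yes |
| Day 5 ± 2, main group | Marked | Treatments current at the contact; no dates | Partly |
| Day 3, nested | Marked | No medication item | No |
| Day 7, nested | Marked | Not named; general wording only | Not explicit |

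**2. What can be missed.** Three other routes record drugs: the Day 1 items (7.2.2), treatment prescribed by study staff (7.2.3), and treatment undertaken for any adverse event, with no restriction on who prescribed it (8.4). The flow charts add unforeseen visits. What remains is a drug begun after the Day 1 visit, not prescribed by study staff and not given for an adverse event. In the main group it must also have been stopped before the contact. In the nested group the loss depends on whether staff follow the 7.2.3 text or the flow chart.

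**3. Illustration: share of later-started courses missed by a question on current use.** Assume that courses of d days start evenly over the w days between Day 1 and the contact, where w = contact day − 1. A course is still running at the contact with probability d/w, so the missed share is 1 − d/w (zero when d ≥ w).

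| Contact | w | d = 1 | d = 2 | d = 3 |
|---|---|---|---|---|
| Day 3 | 2 | 50% | 0% | 0% |
| Day 5 | 4 | 75% | 50% | 25% |
| Day 7 | 6 | 83% | 67% | 50% |

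These shares apply only to the residual group in step 2, not to all drug use.

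**4. Illustration: effect on a comparison in the nested subset.** Assume n = 1,000, adverse-event risk of 10% without the drug and 20% with it (true risk ratio 2.0), true exposure e of 10% to 50%, a share s of users recorded regardless of outcome, and missed users analysed as non-users. The risk in the apparent non-users is then

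[(1 − e) × 0.10 + e(1 − s) × 0.20] / (1 − e·s).

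For e = 0.10 and s = 0.5 this is (0.090 + 0.010)/0.95 = 0.1053, and the observed risk ratio is 0.20/0.1053 = 1.90. For e = 0.50 and s = 0.5 it is (0.050 + 0.050)/0.75 = 0.1333, giving 1.50.

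| Users recorded | Observed risk ratio | Power |
|---|---|---|
| 100% | 2.0 | 80–99% |
| 75% | 1.67–1.95 | 69–92% |
| 50% | 1.50–1.90 | 54–76% |

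Here s refers to all users. Because Day 1 users are recorded, the lower rows apply only if a large part of exposure begins after Day 1. The documents give neither e nor s.

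**The case against.** The strongest reply is that the lists in 7.2.3 are not exhaustive. The Day 7 text also omits the piperaquine sample that section 5.1 and the nested flow chart require, and nobody would conclude that the sample is cancelled. The flow chart is current protocol text and does require medications at Day 3 and Day 7. Sections 10.1 and 10.5 place data capture on study logs and forms that the sponsor develops, and those may ask the full question. This stands for the nested group: the gap there is mainly one of alignment, and loss is a risk rather than a certainty. It is weaker for the main-group item, which is a worded rule limited to current use and not merely silent.

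A reader might infer more than the documents support:

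- **That drugs taken with all three doses are lost.** Section 7.2.2 captures what is in use or prescribed at Day 1, the day of the supervised first dose.
- **That unrecorded users are counted as unexposed.** No such rule is stated, and the definition may lie in the analysis plan. It is only an assumption in the illustration.
- **That the protocol itself shows widespread self-medication after enrolment.** Section 3.3 does say that "use of traditional medicine and left over drugs at home is also common in the study area". The sentence concerns the Kintampo area, one of the seven sites in section 6.3.1, and stands beside a statement about where care is first sought for a child's febrile illness. It is no evidence about drug use after inclusion across the study.

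It is also fair to say that the analysis is described as mainly descriptive, so no formal test depends on this item.

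**Conclusion.** The inconsistency is real and worth correcting, but it is limited. Followed as written, the Day 5 item misses drugs begun after the Day 1 visit and stopped before the contact, unless they were given for an adverse event or prescribed by study staff. The nested Day 3 and Day 7 text should name an item that the flow chart already requires and that a secondary objective needs.

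Under-recording would probably weaken the comparisons of adverse events, and of events of special interest, with concomitant drugs. That direction assumes that recording does not depend on outcome. Because treatment given for an event is recorded by a separate route, the assumption may fail, and without dates a drug taken before an event cannot be told apart from one taken because of it. The size cannot be estimated from the documents: the percentages in the illustration rest on assumed course lengths, exposure and recording rates.

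**What to change.** In section 7.2.3, replace the main-group medication item with: all treatments taken since the inclusion visit, including self-obtained and traditional medicines, with start and stop dates. Add the same item, covering the period since the last visit, to the nested Day 3 list and to the Day 7 text, so that both match the flow charts. Check that the study forms carry the same wording.

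The cost is one reworded item and one or two extra questions at contacts that already take place. No visit, sample or staff is added.

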# On Day 3, ECG recording and plasma sample for PQ will take place twice, i.e. before and 3-4 hours after Eurartesim® administration. The ECG recorded after drug intake will be collected in triplicate.

## 2. LIST OF ABBREVIATIONS

|       |                                                          |
|-------|----------------------------------------------------------|
| ACT   | Artemisinin-based Combination Therapy                    |
| AE    | Adverse Event                                            |
| AESI  | Adverse Event of Special Interest                        |
| AS    | Artesunate                                               |
| BF    | Burkina Faso                                             |
| CHA   | Community Health Agent                                   |
| CRF   | Case Report Form                                         |
| DHA   | Dihydroartemisinin                                       |
| DOT   | Directly Observed Treatment                              |
| ECG   | Electrocardiogram                                        |
| HCP   | Health Care Provider (of the HDSS centre)                |
| HDSS  | Health and Demographic Surveillance System |
| GEP   | Good Epidemiological Practices                           |
| GH    | Ghana                                                    |
| HA    | Health Agent (of the HDSS centre)                        |
| INESS | The INDEPTH Effectiveness and Safety Studies             |
| MA    | Marketing Authorisation                                  |
| MMV   | Medicines for Malaria Venture                            |
| MZ    | Mozambique                                               |
| NMCP  | National Malaria Control Program                         |
| PHP   | Public Health Pharmacy                                   |
| PI    | Principal Investigator                                   |
| PQP   | Piperaquine phosphate                                    |
| RDT   | Rapid Diagnostic Test                                    |
| SAE   | Serious Adverse Event                                    |
| SmPC  | Summary of Products Characteristics                      |
| TZ    | Tanzania                                                 |
| WHO   | World Health Organisation                                |

